#### 2.7.3. Vital Signs

For vital signs, blood pressure, pulse, respiratory rate, and body temperature will be measured. Vital signs will be measured before the scheduled test for each visit in accordance with the clinical trial schedule. Participants will be directed to relax for 5 min and be seated during the measurement.

#### 2.7.4. Physical Examination

Each participant will be physically examined through inspection, palpation, percussion, and auscultation in accordance with the clinical trial schedule to check their health conditions and find any adverse events. Physical examination includes examination of the external appearance, head and neck, chest and lungs, heart, abdomen, urinary and reproductive systems, limbs, musculoskeletal system, nervous system, and lymph nodes.

#### 2.7.5. ECG Test

An ECG test will be performed for all participants at Visits 1, 3, 4, and 5. The examiner will determine whether the ECG results are normal or abnormal. If the results are abnormal, the examiner will record the clinical significance of the findings on the case report form (CRF).

### 2.8. Clinical Assessment

#### 2.8.1. Pain VAS Assessment [20]

Participants will mark their subjective pain level around the hip joint on a scale that ranges from “no pain (0)” to “severe pain (10)”. The examiner will determine the number corresponding to the point marked on the scale and record it to one out of 10 decimal places. To examine the changes in pain VAS at different time points after CF-M801 administration, pain VAS assessment will be performed at Visits 2 and 5.

#### 2.8.2. HHS Assessment [21]

HHSs will be assessed at Visits 2 and 5 to examine the participants’ hip joint function. The highest possible score is 100, and the following domains will be assessed: pain (44 points), gait function (11 points), support devices (11 points), distance walked (11 points), stairs (4 points), putting on shoes (4 points), sitting (5 points), entering public transportation (1 point), presence of deformity (4 points), and hip joint range of motion (5 points).

#### 2.8.3. WOMAC Score Assessment [22]

WOMAC scores will be assessed at Visits 2 and 5 to examine the changes in WOMAC scores after CF-M801 administration and assess participants’ joint function. WOMAC assesses three domains, namely, pain, stiffness, and physical function.

### 2.9. Radiologic Assessment

#### 2.9.1. Measuring Changes in Necrotic Lesion Size

To examine changes in the size of a necrotic lesion in the femoral head following CF-M801 administration, the modified Kerboul index will be measured on mid-coronal and mid-sagittal MRI images acquired during Visits 1 and 5 [24,25].

#### 2.9.2. ARCO Classification [23]

The ARCO classification is an improved version of the Ficat and Arlet classification based on the presence and severity of femoral head collapse and Steinberg classification based on lesion size and progression, which are commonly used to stage ONFH. Two independent examiners will analyze radiographs and MRI of the hip joint during Visit 1 and 5 to examine the changes in the ARCO stage following CF-M801 administration. They will then classify the patients who show changes in the ARCO stage following CF-M801 administration and femoral head collapse using the ARCO classification. Femoral head collapse corresponds to ARCO stage 3.

#### 2.9.3. JIC Classification [26]

The JIC classification classifies ONFH based on the location of the lesion. It is a radiographic classification method with three major types of ONFH and is based on the location of the lesion in respect to the weight-bearing surface. Two independent examiners will examine the changes in the JIC stage after CF-M801 administration by evaluating radiographs and MRI of the femoral region during Visit 1 and 5 and classify the lesions according to the JIC classification.

### 2.10. Data Collection, Management, and Analysis

#### 2.10.1. Data Collection and Management

Informed consent will be obtained from all participants, and all data will be collected according to the visit schedule in Table 2. Any missing values of safety and efficacy data will not be replaced, and, if the subject’s visit date falls outside the planned tolerance range (visit window), the measurement values for that visit will be treated as missing values. The CRFs will be the primary data collection tool for this trial, and all data requested on the CRFs must be recorded. An electronic data capture system (iMediData) will be used to submit data. Information related to trial participants will be kept confidential and stored securely in a separate space with a locking device, only accessible to research personnel. Trial records will be identified only by a coded participant number, and all records that contain the participants’ names or any identifying information will be stored separately. All local databases used for storage of trial data will be password-protected. 

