Of the patients who consent to participate in this clinical trial, those who satisfy the inclusion and exclusion criteria will be assigned to a low-dose (*n* = 3), middle-dose (*n* = 3), and high-dose group (*n* = 3) in the order of their arrival at the facility without random allocation and followed up for 12 weeks. Nine patients will be assigned if no dose-limiting toxicity (DLT) develops up to the highest dose. Depending on the occurrence of DLT, up to 18 patients can be enrolled by applying the 3 + 3 escalation method.

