**Figure 5 pharmaceuticals-17-01366-f005:**
[figure not shown]
A mixture of cell and collagen putty is implanted into the lesion (black arrow), and the autogenous bone chip and cylindrical bone block is inserted into the remaining space in the core tract (white arrow). If there is significant space remaining in the distal portion of the core tract, a cylindrical hydroxyapatite and tri-calcium phosphate block may be inserted (arrowhead).

**Table 1 pharmaceuticals-17-01366-t001:** Gross characterization of the cell therapy.

	Hematopoietic		Mesenchymal		Osteoblast		Angiogenesis
Markers	CD31	CD45	CD73	CD105	RUNX2	COL1A	ANGPT-1
Expression	≤5%	≤5%	≥50%	≥50%	≥5 copies	≥3000 pg/mL	≥2000 pg/mL

**Table 2 pharmaceuticals-17-01366-t002:** Protocol and timeline for outcome assessments.

Period	Screening	Treatment ^(g)^	Follow-Up 1	Follow-Up 2	Study Completion /Dropout ^(i)^
Visit	1	2	3	4	5 ^(i)^
Week	Within-3	0	2	6	12
Visit window (days)	-	Within-3	±3	±7	+7
Written consent form ^(a)^	X				
Demographic information	X				
Body weight and height measurement	X				
Review medical/operation history	X	X ^(h)^			
Review medication history	X	X ^(h)^			
Vital signs ^(b)^	X	X ^(h)^	X	X	X
Physical examination	X	X ^(h)^	X	X	X
Clinical laboratory tests ^(c)^	X ^(C−1), C−2)^		X	X	X ^(C−1)^
ECG test	X		X	X	X
Pregnancy test ^(d)^	X				X
Radiographic examination	X ^(e)^		X	X	X
MRI examination	X				X
ARCO classification	X				X
JIC classification	X				X
Review inclusion/exclusion criteria	X	X			
Patient selection		X			
Group allocation		X			
Core decompression		X			
hUC-Os administration		X			
Pain VAS assessment		X ^(h)^			X
HHS assessment		X ^(h)^			X
WOMAC assessment		X ^(h)^			X
Adverse events assessment		X ^(f)^	X	X	X
Check concomitant drug use		X	X	X	X

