ECG, electrocardiogram; MRI, magnetic resonance imaging; ARCO, Association Research Circulation Osseous; JIC, Japanese Investigation Committee; hUC-Os, human umbilical cord-derived osteoblasts; VAS, visual analog scale; HHS, Harris hip score; WOMAC, Western Ontario and McMaster Universities. ^(a)^ Written consent can be obtained from participants before the screening visit. ^(b)^ For vital signs, pulse, blood pressure, and body temperature will be measured. At Visit 2, vital signs will be measured before hUC-O administration. ^(c)^ For screening tests, test results obtained within 4 weeks after a visit can be used. A retest may also be performed once at the discretion of a researcher during the screening period. The following parameters are assessed during the laboratory tests. Blood test: red blood cell (RBC) count, hemoglobin, hematocrit, platelet count, white blood cell (WBC) count, WBC differential count (neutrophil, lymphocyte, monocyte, eosinophil, and basophil), and erythrocyte sedimentation rate; Blood chemistry test: total protein, albumin, total bilirubin, aspartate aminotransferase or alanine transaminase, gamma-glutamyl transpeptidase, blood urea nitrogen, creatinine, glucose, alkaline phosphatase, total cholesterol, triglyceride, uric acid, C-reactive protein, panel reactive antibody ^(C−1)^, virus infection test (human immunodeficiency virus antigen/antibody, hepatitis B surface antibody, anti-hepatitis C virus antibody, venereal disease research laboratory) ^(C−2)^; Urinalysis: protein (albumin), glucose, ketones, WBC, RBC. ^(d)^ A serum or urine human chorionic gonadotropin test will be performed for women of childbearing age except for those who have been sterilized or are menopausal. Women of childbearing age refer to women who have had their first period, have not been successfully surgically sterilized (via hysterectomy, bilateral tubal ligation, or bilateral oophorectomy), and are not menopausal. Menopause is defined as not having a period for >12 months after the final menstrual period. ^(e)^ Test results obtained within 4 weeks after screening can be used. ^(f)^ Acute adverse events that occur within 3 days after hUC-O administration will be investigated. ^(g)^ Patients will be hospitalized starting 1 day before hUC-O administration and will be monitored throughout the hospitalization period for adverse events. ^(h)^ Performed within 3 days and restrict intake of analgesics within 1 day before hUC-O administration. ^(i)^ For participants who were withdrawn following the group allocation, the procedures scheduled for the last visit will be performed.

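### The visit-window rule sets observed safety measurements to missing because of their date; the exposure is greatest for the single post-treatment panel reactive antibody result at Visit 5

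*Protocol article*

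**What the plan says.** Section 2.10.1 (Data Collection and Management) handles missing data and visit windows in one sentence. Its first half reads "Any missing values of safety and efficacy data will not be replaced". Its second half adds that if a participant's "visit date falls outside the planned tolerance range (visit window), the measurement values for that visit will be treated as missing values". Nothing in the section limits the second half to efficacy.

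Table 2 sets the windows: "Visit window (days) - Within-3 ±3 ±7 +7", for Visits 1 to 5 in order. Visit 5 is at week 12 and its window has no minus side. Its column is headed "Study Completion /Dropout", and footnote (i) says: "For participants who were withdrawn following the group allocation, the procedures scheduled for the last visit will be performed". No separate window is given for a withdrawal visit.

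Section 2.7.2 schedules PRA at Visits 1 and 5 only. The Discussion lists PRA among the tests that serve the main safety objectives.

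On numbers, Section 2.3 says "Nine patients will be assigned if no dose-limiting toxicity (DLT) develops up to the highest dose", three per dose, and that "up to 18 patients can be enrolled by applying the 3 + 3 escalation method".

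**The concern.** A missing-data rule normally says what to do about values that were not obtained. This one also turns obtained values into missing ones, and it does so for safety data in a trial whose main concern is safety (Section 2.1). A laboratory, ECG, vital-sign or PRA result keeps its meaning for safety when the participant attends a few days off schedule.

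PRA is the measurement most at stake. It is the planned check for an immune reaction to allogeneic cells, and each participant has one post-treatment value. If that value is set aside, no other planned post-treatment PRA can stand in for it. Laboratory tests, vital signs, physical examination and ECG are also done at Visits 3 and 4, so losing one visit costs less there.

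The rule also fits poorly with footnote (i), which orders the last-visit procedures for participants who leave early. On a literal reading the plan collects those results and then excludes them.

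**Working it through.** **Group sizes.** From Section 2.3: 3 doses × 3 = 9 participants. At 6 per dose, 3 × 6 = 18. Both agree with the article.

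**Windows in study days** (Table 2, counting administration as day 0):

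| Visit | Planned day | Window | Days inside | Number of days |
|---|---|---|---|---|
| 3 | 14 | ±3 | 11–17 | 7 |
| 4 | 42 | ±7 | 35–49 | 15 |
| 5 | 84 | +7 | 84–91 | 8 |

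The windows cover 7 + 15 + 8 = 30 of the 91 days after administration. None of days 1 to 83 lies in the Visit 5 window. A final visit on day 83 therefore misses it by one day. A withdrawal visit before week 12 also falls outside it, if that window is taken to govern withdrawal visits.

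**What one missed Visit 5 window removes.** It removes one participant's Visit 5 measurements. For measures whose only post-treatment assessment is Visit 5 (PRA, MRI, ARCO, JIC, pain VAS, HHS and WOMAC), that is 1/3 = 33% of the dose group's post-treatment values, or 1/6 = 17% in a group of six.

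**Effect on the chance of seeing a signal.** Suppose a PRA result is classed as abnormal or not, with true abnormal rate p (assumed; the article gives none). The chance that n evaluable participants show at least one abnormal result is 1 − (1 − p)^n:

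| p (assumed) | n = 3 | n = 2 | n = 6 | n = 5 |
|---|---|---|---|---|
| 10% | 27.1% | 19.0% | 46.9% | 41.0% |
| 20% | 48.8% | 36.0% | 73.8% | 67.2% |
| 30% | 65.7% | 51.0% | 88.2% | 83.2% |
| 50% | 87.5% | 75.0% | 98.4% | 96.9% |

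After zero abnormal results, the one-sided 95% upper bound on the true rate is 1 − 0.05^(1/n). This is 63.2% with three evaluable and 77.6% with two.

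**How often this might happen.** The article gives no rate of out-of-window visits. If each Visit 5 misses its window independently with probability q, the chance that at least one of nine is affected is 1 − (1 − q)^9. This gives 37.0%, 61.3% and 86.6% for assumed q of 5%, 10% and 20%. These figures show the range only. They depend wholly on q and on independence.

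**The case against.** Several stronger readings are tempting, and the article does not support them.

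- **That the data are thrown away.** Section 2.10.1 also requires all data requested on the case report forms to be recorded. The values exist; they are treated as missing in analysis.
- **That the main safety result or the dose-escalation decisions are compromised.** Section 2.7.1 collects adverse events at regular or additional visits, by interview and from history. Section 2.7 records abnormal findings after administration as adverse events when they meet that definition, with no window condition. DLT is defined through adverse events (Section 2.6). A clinically significant finding at an early or late visit can therefore still reach the adverse-event record. This stands, and it limits the point to measured values. It does not clearly cover PRA, because the article does not say whether a PRA rise alone would count as an adverse event.
- **That one missed window removes a participant.** It removes one visit's measurements. The participant stays in the adverse-event and DLT counts and in the other visits' summaries.
- **That every withdrawal visit is certainly lost.** A withdrawal visit is triggered by an event and has no planned date of its own. The article does not say outright that the week 12 window applies to it. The literal reading of Table 2 with footnote (i) leads there, but the firm statement is that the handling of withdrawal data is unresolved.
- **That participants who leave early or attend off schedule are those most likely to have a problem, so the summary is biased towards looking clean.** This is possible, but nothing in the article shows it.

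It can also be said that excluding out-of-window values from exploratory, purely descriptive efficacy summaries is a legitimate choice made in advance. That is fair, and the efficacy side is closer to preference than error.

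The objection does not remove the rule itself. It is stated in the article, it names safety data, and an analysis plan that follows it would inherit it.

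**Conclusion.** The point holds for safety measurements: laboratory tests, PRA, vital signs and ECG. Followed as written, the rule takes observed values out of the safety summaries on the ground of their date alone. Visit 5 is the weak spot, because an open minus side meets the only post-treatment PRA. The size is 1 of 3 for the affected dose's PRA summary, or 1 of 6 after expansion. At an assumed 20% abnormal rate, going from three to two evaluable lowers the chance of seeing any abnormal result from 48.8% to 36.0%.

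This rests on counting administration as day 0 and on the rule being applied as worded. For withdrawal visits it also rests on the Visit 5 window applying to them. Because adverse events and DLTs have a separate route and the values remain recorded, this should be fixed but does not by itself undermine the trial's conclusions on DLT.

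**What to change.** Amend the window sentence in Section 2.10.1, and carry the change into the analysis plan, so that:

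1. All observed safety measurements, including those from out-of-window and withdrawal visits, are kept in the safety listings and summaries by actual study day.
2. Visit windows serve only to assign by-visit labels.
3. Results obtained under Table 2 footnote (i) are stated to be included.
4. For exploratory efficacy, out-of-window values are at least listed with their study day, even if the by-visit summaries keep to in-window values.

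The cost is a short text change with no extra data collection. The downside is that some by-visit safety summaries will hold values from slightly different days, which the listing by study day makes visible.

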#### 2.10.2. Data Analysis

This clinical trial was planned as a phase 1 clinical trial using a 3 + 3 dose escalation method, and, because three subjects will be assigned to each group, it is not appropriate for statistical processing. Thus, data analysis will be conducted in the following manner. For the data collected in this trial, continuous data will be presented as descriptive statistics (number of patients, mean, standard deviation, minimum, median, maximum) and categorical data will be presented as frequencies and percentages.

## 3. Discussion

Cell therapy is becoming more popular as a means to restore deficient local cell populations due to disease or injury. ONFH is associated with a decrease in progenitor cells in the femoral head that can influence bone repair due to alteration of intramedullary vascularity [31,32]. MSCs are multipotent cells that can differentiate into fibroblastic, osteogenic, myogenic, adipogenic, and reticular cells [32,33] and are mainly harvested from bone marrow, adipose tissue, and umbilical cord. Most of previous studies used bone marrow-derived MSCs (BMSCs) and showed satisfactory results [11,12,15,34,35]. A previous study with the longest follow-up duration of 25 years, which administered BMSCs to one side while performing core decompression alone to opposite side in 125 patients with bilateral ONFH, reported that the BMSC group had significantly lower THA conversion rates than the core decompression alone group (24% vs. 76%, *p* < 0.001) [15]. However, considering the natural course of ONFH according to the location and size of the lesion [1], the study was limited because it did not analyze the size and location of lesion before the procedure and it is difficult to evaluate the accurate effect of the BMSCs. Moreover, according to a recent systemic review, standardization is still insufficient for the collection, cell-processing, and delivery method of MSCs [16].

In animal experiments, hUCMSCs had an effect applicable to ONFH treatment. Kuang et al. [36] reported that hUCMSCs inhibited osteocyte apoptosis in steroid-induced ONFH rat models, and You et al. [19] showed that hUCMSCs promoted angiogenesis in a rat bronchopulmonary dysplasia model. In canine experiments comparing hUCMSCs with MSCs derived from adipose tissue and bone marrow, hUCMSCs showed higher osteogenic potential than other cell sources [18]. To the best of our knowledge, there has been one study that applied hUCMSCs to ONFH patients. Chen et al. [37] performed ‘intra-arterial’ injection of hUCMSCs on nine patients with ONFH at ARCO stage 2 to 3A and reported increased oxygen delivery at 3 days and reduced extent of ONFH at 2 years postoperatively. However, intra-arterial injection requires a higher dose than direct implantation into the lesion, and safety has not been established yet [13].

This study is the first clinical trial conducted for treatment of early-stage ONFH by direct intralesional application of hUC-O. In addition, this study will assess the clinical outcomes and evaluate the extent of necrotic lesions using MRI before and after treatment. We are also fully aware of the limitations of this study. First, this study is non-blinded and may have selection and detection biases. Second, this study is limited because of the short follow-up duration of 12 weeks. Indeed, 12 weeks are too short to conclude the efficacy of new treatment. However, this is a phase I clinical trial in which safety is the main concern and which tests the adverse effects, best dose, and timing of a new treatment [38]. The main objectives of this study are to evaluate any adverse events and to confirm the safety of administered hUC-Os through vital signs, physical examination, ECG tests, and laboratory tests, including PRA tests, to monitor allograft immune reactions following allogeneic cell transplantation [39]. Since the exploratory efficacy is included in this study as well, the minimum observation period of 12 weeks was required from the Korea Food and Drug Administration. In addition, long-term follow-up to 5 years will be conducted on the subjects enrolled, and all data will be submitted to the Korea Food and Drug Administration as well.

Nevertheless, we believe that this phase I clinical trial to confirm the safety and evaluate exploratory effects of hUC-Os on early-stage ONFH will lead to improve our current knowledge of cell therapy and add a new strategy to preserve joints for those suffering from ONFH.

## Figures and Tables

**Figure 1 pharmaceuticals-17-01366-f001:**
[figure not shown]
A guide pin is inserted under fluoroscopic guidance towards the necrotic area for a core tract. (**A**) Anterior posterior view. (**B**) Lateral view.

**Figure 2 pharmaceuticals-17-01366-f002:**
[figure not shown]
To guide a following hollow reamer, an entry hole is created using a cannulated solid reamer along the guide pin (**A**), and an autogenous bone chip is collected during reaming (**B**).

**Figure 3 pharmaceuticals-17-01366-f003:**
[figure not shown]
A core tract is created for core decompression using a hollow biopsy cannula (**A**). During this procedure, a cylindrical autogenous bone block is collected, of which a proximal necrotic portion will be sent for pathologic evaluation and a distal viable portion will be implanted as a bone plug after stem cell insertion (**B**).

**Figure 4 pharmaceuticals-17-01366-f004:**
[figure not shown]
A curette is inserted to remove the necrotic lesion (**A**), followed by washing the necrotic bone debris (**B**).

**Figure 5 pharmaceuticals-17-01366-f005:**
[figure not shown]
A mixture of cell and collagen putty is implanted into the lesion (black arrow), and the autogenous bone chip and cylindrical bone block is inserted into the remaining space in the core tract (white arrow). If there is significant space remaining in the distal portion of the core tract, a cylindrical hydroxyapatite and tri-calcium phosphate block may be inserted (arrowhead).

**Table 1 pharmaceuticals-17-01366-t001:** Gross characterization of the cell therapy.

	Hematopoietic		Mesenchymal		Osteoblast		Angiogenesis
Markers	CD31	CD45	CD73	CD105	RUNX2	COL1A	ANGPT-1
Expression	≤5%	≤5%	≥50%	≥50%	≥5 copies	≥3000 pg/mL	≥2000 pg/mL

**Table 2 pharmaceuticals-17-01366-t002:** Protocol and timeline for outcome assessments.

Period	Screening	Treatment ^(g)^	Follow-Up 1	Follow-Up 2	Study Completion /Dropout ^(i)^
Visit	1	2	3	4	5 ^(i)^
Week	Within-3	0	2	6	12
Visit window (days)	-	Within-3	±3	±7	+7
Written consent form ^(a)^	X				
Demographic information	X				
Body weight and height measurement	X				
Review medical/operation history	X	X ^(h)^			
Review medication history	X	X ^(h)^			
Vital signs ^(b)^	X	X ^(h)^	X	X	X
Physical examination	X	X ^(h)^	X	X	X
Clinical laboratory tests ^(c)^	X ^(C−1), C−2)^		X	X	X ^(C−1)^
ECG test	X		X	X	X
Pregnancy test ^(d)^	X				X
Radiographic examination	X ^(e)^		X	X	X
MRI examination	X				X
ARCO classification	X				X
JIC classification	X				X
Review inclusion/exclusion criteria	X	X			
Patient selection		X			
Group allocation		X			
Core decompression		X			
hUC-Os administration		X			
Pain VAS assessment		X ^(h)^			X
HHS assessment		X ^(h)^			X
WOMAC assessment		X ^(h)^			X
Adverse events assessment		X ^(f)^	X	X	X
Check concomitant drug use		X	X	X	X

ECG, electrocardiogram; MRI, magnetic resonance imaging; ARCO, Association Research Circulation Osseous; JIC, Japanese Investigation Committee; hUC-Os, human umbilical cord-derived osteoblasts; VAS, visual analog scale; HHS, Harris hip score; WOMAC, Western Ontario and McMaster Universities. ^(a)^ Written consent can be obtained from participants before the screening visit. ^(b)^ For vital signs, pulse, blood pressure, and body temperature will be measured. At Visit 2, vital signs will be measured before hUC-O administration. ^(c)^ For screening tests, test results obtained within 4 weeks after a visit can be used. A retest may also be performed once at the discretion of a researcher during the screening period. The following parameters are assessed during the laboratory tests. Blood test: red blood cell (RBC) count, hemoglobin, hematocrit, platelet count, white blood cell (WBC) count, WBC differential count (neutrophil, lymphocyte, monocyte, eosinophil, and basophil), and erythrocyte sedimentation rate; Blood chemistry test: total protein, albumin, total bilirubin, aspartate aminotransferase or alanine transaminase, gamma-glutamyl transpeptidase, blood urea nitrogen, creatinine, glucose, alkaline phosphatase, total cholesterol, triglyceride, uric acid, C-reactive protein, panel reactive antibody ^(C−1)^, virus infection test (human immunodeficiency virus antigen/antibody, hepatitis B surface antibody, anti-hepatitis C virus antibody, venereal disease research laboratory) ^(C−2)^; Urinalysis: protein (albumin), glucose, ketones, WBC, RBC. ^(d)^ A serum or urine human chorionic gonadotropin test will be performed for women of childbearing age except for those who have been sterilized or are menopausal. Women of childbearing age refer to women who have had their first period, have not been successfully surgically sterilized (via hysterectomy, bilateral tubal ligation, or bilateral oophorectomy), and are not menopausal. Menopause is defined as not having a period for >12 months after the final menstrual period. ^(e)^ Test results obtained within 4 weeks after screening can be used. ^(f)^ Acute adverse events that occur within 3 days after hUC-O administration will be investigated. ^(g)^ Patients will be hospitalized starting 1 day before hUC-O administration and will be monitored throughout the hospitalization period for adverse events. ^(h)^ Performed within 3 days and restrict intake of analgesics within 1 day before hUC-O administration. ^(i)^ For participants who were withdrawn following the group allocation, the procedures scheduled for the last visit will be performed.
